**LIST OF ABBREVIATIONS AND RELEVANT DEFINITIONS**

| ABR | ABR form, General Assessment and Registration form, is the application form that is required for submission to the accredited Ethics Committee (In Dutch, ABR = Algemene Beoordeling en Registratie) |
| --- | --- |
| AE | Adverse Event |
| AR | Adverse Reaction |
| BMI | Body Mass Index |
| CA | Competent Authority |
| CCMO | Central Committee on Research Involving Human Subjects; in Dutch: Centrale Commissie Mensgebonden Onderzoek |
| CV | Curriculum Vitae |
| DSMB | Data Safety Monitoring Board |
| EU | European Union |
| EudraCT | European drug regulatory affairs Clinical Trials |
| GCP | Good Clinical Practice |
| IB | Investigator’s Brochure |
| IC | Informed Consent |
| IMP | Investigational Medicinal Product |
| IMPD | Investigational Medicinal Product Dossier |
| METC | Medical research ethics committee (MREC); in Dutch: medisch ethische toetsing commissie (METC) |
| RCT | Randomized Controlled Trial |
| (S)AE | (Serious) Adverse Event |
| SPC | Summary of Product Characteristics (in Dutch: officiële productinfomatie IB1-tekst) |
| Sponsor | The sponsor is the party that commissions the organisation or performance of the research, for example a pharmaceutical  company, academic hospital, scientific organisation or investigator. A party that provides funding for a study but does not commission it is not regarded as the sponsor, but referred to as a subsidising party. |
| SUSAR | Suspected Unexpected Serious Adverse Reaction |
| Triple P | Positive Parenting Program |
| Wbp | Personal Data Protection Act (in Dutch: Wet Bescherming Persoonsgevens) |
| YHC | Youth Health Care |
|  |  |
| WMO | Medical Research Involving Human Subjects Act (in Dutch: Wet Medisch-wetenschappelijk Onderzoek met Mensen |
| ZonMW | The Netherlands Organisation for Health Research and Development |

**SUMMARY**

**Rationale:** Overweight and obesity are already prevalent in 4 to 8-year-old children. Obesity-inducing behaviours in young children have been found to track throughout the life span. Acknowledging the lack of effective interventions aimed at children aged 4 to 8-year-old, the current study aims at executing an effectiveness study in which a lifestyle intervention aimed at the parents of 4 to 8-year-old children is tested.

**Objective**: The main objective is to evaluate the effectiveness of Lifestyle Triple P.

**Study design:** The design of the current study is a Randomized Controlled Trial (RCT)

**Study population:** The research population consists of 288 participants (96 overweight and obese 4 to 8-year-old children and their parents).

**Intervention (if applicable)**: The lifestyle intervention, called Lifestyle Positive Parenting Program (Lifestyle Triple P), is aimed at parents of overweight and obese children. The intervention will take 14 weeks, consisting of eight weekly 120-minute parental group training sessions, two individual telephone sessions, one parental group training sessions, two individual telephone sessions and a final parental group training session. Triple P is an evidence-based preventively oriented parenting and family support strategy, based on social learning principles. Active skills training methods are employed to help parents acquire new knowledge and skills. The control condition receives two information leaflets (one about healthy nutrition and physical activity, and one about positive parenting), a Time Machine (an electronic screen time manager) and a web-based tailored feedback about providing a good parental example for your child regarding diet and physical activity.

**Main study parameters/endpoints:** The main study parameter is children’s body composition, determined by BMI z-score (calculated by weight, height, age and gender), waist circumference, and fat mass (assessed by biceps and triceps skinfold and deuterium dilution). Secondary study parameters are children’s lifestyle (snacking behaviour, soft-drink consumption, fruit-and vegetable consumption and physical activity), parental body composition (BMI, parental fat mass), parental physical activity level, parenting self-efficacy and parenting style.

**Nature and extent of the burden and risks associated with participation, benefit and group relatedness:** The intervention which the parents of the children receive will take 14 weeks and consists of ten parental group training sessions, and four individual telephone sessions. Furthermore, the body composition of the children and parents (i.e. length, weight, waist circumference, biceps and triceps skinfolds) is measured, children and their parents are asked to wear an Actigraph accelerometer for one week and parents are asked to fill out a questionnaire at baseline, 14 weeks follow-up and 12 months follow-up. Additionally, children’s fat mass is also estimated at baseline and 12 months follow-up using deuterium, the gold standard. Participation in the current study is voluntary and without any risks.

# INTRODUCTION AND RATIONALE

Overweight and obesity are having an increasing global public health impact worldwide, also in the Netherlands (1). Overweight and obesity are already present in 4 to 8-year-old children (12.4% and 3.1% of the Dutch children respectively) (2), and young children already show obesity-inducing behaviours that may track throughout the lifespan (3, 4). Young children have a relatively short history of unhealthy habits, which makes it easier to change these behaviours than in an adult population. However, relatively few studies have been aimed at the implementation and effectiveness of obesity prevention interventions in children aged 4-8 years (5-8). An example of an obesity intervention which starts early in life is described in Abée et al. (9), in which parents of babies in the second week after birth receive recommendations related to stimulating motor development and increasing physical activity, from a nurse in the Well Baby Clinic. To date, the results of this intervention have not been published (9).

# A home-based intervention targeting overweight children aged 4 to 8-years-old may help parents to learn how to provide a positive environment for their children (10, 11). Therefore, last year we implemented a home-based intervention based on the Positive Parenting Programme (Triple P) (12), which we tested in a pilot study (MEC 08-3-092). The Positive Parenting Program (Triple P) is a preventively-oriented parenting and family support strategy (12), which is based on social learning principles and is aimed at designing more positive environments for children. Triple P adopts a system-contextual or ecological perspective in supporting parents. The program aims to prevent severe behavioural, emotional and developmental problems in children by enhancing the knowledge, skills and confidence of parents. Triple P incorporates five levels of intervention on a tiered continuum of increasing strength for parents of children and adolescents. Level 1 mainly uses mass media resources to increase community awareness of parenting resources and the receptivity of parents to participating in programs. The intensity of the programme increases towards Level 5, which represents an enhanced behavioural family intervention program for families where child behaviour problems persist (12). Level 4 Triple P matches the aims of the current intervention, and was therefore applied. It consists of a parent training program for children with behavioural difficulties or who are at risk of developing such problems, which can be offered either individually or in a group of parents. The intervention we developed consisted thus of Level 4 Triple P with additional sessions focusing on environmental influences on energy balance-related behaviours in children.

In the pilot study (MEC 08-3-092) it was tested 1) whether this intervention was applicable to parents of 4-year-old overweight children and 2) whether the recruitment for the intervention was feasible for primary care youth health care (YHC) professionals to incorporate in their daily practice. The most important results were that:

1. Parents indicated in a focus group that they were very enthusiastic about the program, they liked the program sessions, felt comfortable in the group, they learned a lot and they reported that they already experienced a change in the behaviour of their child. However parents indicated that they preferred more sessions and more general information about healthy eating and physical activity.
2. YHC professionals faced various difficulties in the recruitment of overweight children via the Dutch YHC. As a result, we have adapted the recruitment procedure for the current study (see Study Design).

While we were conducting our pilot study, the results of an RCT performed by the University of Queensland evaluating the efficacy of Lifestyle Triple P, became available (13, 14). Lifestyle Triple P is very similar to the program we initially developed, it is also a modification of Level 4 Group Triple P, with additional sessions focusing on nutrition and physical activity, targeting families with overweight or obese children. Their study showed that Lifestyle Triple P resulted in increased parenting self-efficacy, reduced effective parenting and decreased children’s BMI and body fat of children aged 4 to 11-years old (13). We have studied the Lifestyle Triple P intervention materials in detail and we concluded that the intervention is very similar to the intervention we piloted. It differs from our pilot intervention on some points (i.e. more sessions, and more emphasis on knowledge transfer). These were exactly the points that were identified in our pilot study that could improve our intervention. It would be valuable to test whether the Lifestyle intervention is effective in the Netherlands (after translation).

The aim of the current study is therefore to test the effectiveness of Lifestyle Triple P in the Netherlands.

# OBJECTIVES

Primary Objective: The primary objective is to evaluate the effectiveness of the Lifestyle Triple P intervention in 4 to 8-year-old overweight children on their BMI z-score, and fat mass.

Secondary Objective(s): The secondary objectives of the current study are to determine the effect of the intervention on children’s lifestyle (snacking behaviour, soft-drink consumption, fruit-and vegetable consumption and physical activity), parental BMI, parental fat mass, parental physical activity level, parenting self-efficacy and parenting style.

# STUDY DESIGN

The design of the current study will be a Randomized Controlled Trial, in which the effectiveness of the Lifestyle Triple P intervention will be tested. The complete study will take 18 months.

In total, 288 parents and children will be recruited. Parents will be recruited in two ways: 1) via the Dutch Youth Health Care and 2) via mass media.

1) Parents of children who are, according to medical documents of the YHC (Municipal Health Service; GGD) overweight or obese (and there is no organic cause for the overweight) will be approached by telephone by health educators working in our project (also working as youth nurses at the YHC South-Limburg). In this telephone call, parents are provided with information about the intervention. In case parents prefer to get the information about the research face-to-face, a home visit can be planned. After the parents received oral information about the research, they also receive written information in the form of a patient information letter. Parents can decide their participation within two weeks. They confirm their participation by filling out an informed consent form.

This way of recruiting the parents fits within the standard procedures of the YHC. Following these standard procedures, the medical documents of children are screened for overweight and obesity using the weight-by height curve on the 1997 Dutch growth study charts. When the weight is ≥ 1 SDS, the BMI is calculated and by using the international BMI cut-off points of Cole et al. (15) (which are based on six large nationally representative cross sectional surveys on growth including the Netherlands), the child is labelled ‘normal weight’, ‘overweight, not obese’ or ‘obese’. Overweight and obese children are approached for an extra consult with the YHC physician. In our proposed recruitment strategy, they are contacted by the health educators of our project (youth nurses) to participate in the study. In case parents do not want to participate in the current study, they are still offered the extra consultation with the physician.

2) A website is developed where interested parents can apply for more detailed information and where they can register when they want to be approached for participation in the research. Through a mass media campaign, which consists of the dissemination of a brochure and a poster (via e.g., schools, day care centers, health centers), and advertisements in local newspapers, people will become aware of the program and the website. Families who register for participation in the program will by phoned by our health educators to provide them with more detailed information about the research. In case parents prefer to get the information about the research face-to-face, a home visit can be planned. After the telephone call or home visit, parents receive a patient information letter. Parents can decide their participation in the research within two weeks by filling out an informed consent form.

After they decided to participate in the research, participants (both parents and children) are asked to come to the Municipal Health Service (GGD) where baseline measurements are performed by the research team of the current study. Children and parents will be measured for their weight, height, skinfold thickness (biceps and triceps), and waist circumference. Materials and instructions for measuring deuterium dilution (used for measuring children’s body composition) will be provided to the parents, which they have to send back by mail within one week. Children and parents are asked to wear an Actigraph accelerometer for 7 days. Parents are asked to return a baseline questionnaire which their received one week earlier by mail.

After the baseline measurements, parents are randomly assigned to either the intervention or the control condition. Participants in the intervention condition receive a 14-week intervention which consists of ten parental group training sessions, and four individual telephone sessions for parents. Participants in the control condition receive two information leaflets (one about healthy nutrition and physical activity (Dutch Nutrition Centre; Voedingscentrum) and one about positive parenting (Netherlands Youth Institute; NJi)), a Time Machine (an electronic screen time manager), and web-based tailored feedback about providing a good parental example for your child regarding diet and physical activity (Dutch Nutrition Centre; Voedingscentrum).

Parents of both conditions receive a follow-up questionnaire by mail after the intervention. They are again asked to visit the Municipal Health Service (GGD) where the child and both parents will be measured for anthropometric measurements (not deuterium) by the research team of the current study. Parents and children will be asked to wear an Actigraph accelerometer for 7 days. A final visit where all measurements are conducted, will take place 12 months after baseline (see flow-chart). During this visit, again materials and instructions are provided for measuring deuterium dilution, which they have to send back by mail within one week.

Flow chart 1: RCT to test the effectiveness of Lifestyle Triple P aimed at the prevention of excessive weight gain in overweight children

| **Recruitment of participants** | |
| --- | --- |
| **Via youth health care** | **Via mass media** |
| Medical documents children (YHC) are screened to indicate overweight and obese children | Mass media makes people aware of the intervention and a website of the project |
| **↓** | **↓** |
|  | At the project website people are provided with information about the intervention. People can apply for more information about the intervention. |
|  | **↓** |
| Parents of children who are labeled as overweight, or obese are approached by telephone by a specialized health educator who provides information about the intervention to the parents | Parents of children who registered for more information are approached by telephone to assure that they are eligible for participation and to provide them with more information |
| **↓** | **↓**. |
| Optional: the health educator provides information during a home visit. | Optional: the health educator provides information during a home visit |
| **↓** | **↓** |
| Parents receive the patient information letter and informed consent form | Parents receive the patient information letter and informed consent form |
| **↓** | **↓** |
| If the parents are willing to participate (they have two weeks to decide), they are both asked to sign for informed consent | If the parents are still willing to participate(they have two weeks to decide), they are both asked to sign for informed consent |
| **↓** | **↓** |
| **Baseline measurements** | |
| **Parents** | **Children** |
| Baseline questionnaire parents, anthropometric measurements and Actigraph accelerometer | Anthropometric measurements (including deuterium dilution) and Actigraph accelerometer |
| **Randomization (on individual level) to one of the two conditions** | |
| **Intervention condition (N = 48)** | **Control condition (N = 48)** |
| 8 parental group training sessions (week 1-8)  **↓**  2 individual telephone sessions (week 9-10)  **↓**  1 parental group training sessions (week 11)  **↓**  2 individual telephone sessions (week 12-13)  **↓**  1 final parental group training session (week 14) | Parents receive a Time Machine, web-based tailored feedback about providing a good parental example for your child regarding diet and physical activity, and two leaflets: one about healthy nutrition and physical activity and one about positive parenting. |
| **Posttest measurements (immediately after the intervention, 14 weeks after baseline)** | |
| **Parents** | **Children** |
| Follow-up questionnaire, follow-up anthropometric measurements and Actigraph accelerometer | Follow-up anthropometric measurements (not deuterium dilution) and Actigraph accelerometer |
| **Posttest measurements (12 months after baseline)** | |
| **Parents** | **Children** |
| Follow-up questionnaire parents, follow-up anthropometric measurements and Actigraph accelerometer | Follow-up anthropometric measurements (including deuterium dilution) and Actigraph accelerometer |

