# STUDY POPULATION

## Population (base)

The research population will consist of 96 child-parents triads (total 288 participants). Parents of children aged 4 to 8 years are eligible for participating when their child is considered ‘overweight or obese’. The sample is expected to include relatively many children of low socio-economic status and ethnic minorities. This sample is drawn from medical reports of 2600 children in the Westelijke Mijnstreek and Eastern South Limburg, who are aged 4-8 years. Of these children, about 12.4% is overweight and 3.1% is obese, and 50% is expected to participate in the program. Therefore 9 months are planned to recruit parents of 96 4 to 8-year-old children

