## Sample size calculation

The expected difference between the intervention and control condition is 0.30 BMI-points over 6 months (based on Robinson (16)). This difference would imply and approximated relative weight loss of 1480 grams per year in the experimental condition (1020 grams weight gain versus 2500 grams weight gain in the control condition). Maintained behavioural changes would then lead a child in the experimental condition to a weight corresponding to the 50th percentile when it reaches the age of eight years.

The expected difference between both conditions would require a sample of 38 families in each condition to detect this difference with a power of .90 and p<.05. Adjusting for attrition, a total of 96 families will be randomly assigned to the intervention of control condition. Given an expected 10% of children to meet the inclusion criteria, 2600 4-year-olds that are aged 4-years old, and 50% participation-rate, recruitment is expected to take 9 months. Unless conflicting results from the pilot study, group sessions will consist of 8 families, resulting in 6 groups in the intervention condition.

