# METHODS

## Study parameters/endpoints

### Main study parameter/endpoint

The primary objective of this study is to test the effectiveness of the intervention in terms of preventing overweight and obese children from excessive weight gain. The main study parameter is children’s body composition, determined by BMI z-score (calculated by weight, height, age and gender), waist circumference, and fat mass (assessed via biceps and triceps skinfold and deuterium). BMI, waist circumference, and skinfold is measured at baseline, 14 weeks (directly following the intervention) and 12 months follow-up. Deuterium is measured only at baseline and 12 months follow-up.

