## End of study report

The investigator will notify the accredited METC of the end of the study within a period of 8 weeks. The end of the study is defined as the last home visit.

In case the study is ended prematurely, the investigator will notify the accredited METC, including the reasons for the premature termination.
 Within one year after the end of the study, the investigator/sponsor will submit a final study report with the results of the study, including any publications/abstracts of the study, to the accredited METC.

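### The stated 18-month study duration contradicts the protocol's own 9 months of recruitment plus a final visit 12 months after baseline, which needs at least 21 months

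*Protocol*

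**What the plan says.** - **Total duration.** Study design: "The complete study will take 18 months".
- **Recruitment.** Population (base): "Therefore 9 months are planned to recruit parents of 96 4 to 8-year-old children". Sample size calculation: "recruitment is expected to take 9 months".
- **Follow-up.** Study design: "A final visit where all measurements are conducted, will take place 12 months after baseline". The summary, flow chart 1 and the main endpoint section give the same 12-month point. The baseline measurements come after the family has agreed to take part.
- **Fat mass by deuterium.** Main study parameter/endpoint: "Deuterium is measured only at baseline and 12 months follow-up". The measurement list under Study procedures instead gives baseline and 6 months.
- **Recruitment inputs.** Population (base) takes 2600 children aged 4 to 8, of whom 12.4% are overweight and 3.1% obese. Sample size calculation takes 2600 four-year-olds: "Given an expected 10% of children to meet the inclusion criteria". Both assume 50% participation.
- **End of study.** End of study report: "The end of the study is defined as the last home visit".

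**The concern.** Each family's 12-month clock starts at its own baseline, which cannot precede its recruitment. The total duration must therefore cover the whole recruitment period and then a full year for the last family. Eighteen months covers a year of follow-up only for families whose baseline falls in the first 6 months, while recruitment is planned to run for 9. No section says that the 18 months excludes recruitment, or that late entrants are followed for less than a year.

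If a schedule were built on the stated figure, late families would have no 12-month BMI z-score. They would also have no follow-up deuterium value at all, because deuterium has only one post-baseline measurement in the main endpoint section. Fat mass is named in the primary objective.

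**Working it through.** **Inputs from the protocol:** recruitment 9 months; follow-up 12 months from baseline; stated total 18 months; 96 families randomised (48 per arm); 38 per arm required.

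**1. The 9-month recruitment figure.** From the Sample size inputs: 2600 × 0.10 × 0.50 = 130 families. If 2600 is read as a yearly flow (an assumption), 96 / 130 × 12 = 8.9 months, so the 9 months reproduces.

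From the Population inputs: 12.4% + 3.1% = 15.5%, and 2600 × 0.155 × 0.50 = 201.5 families. On the same reading, 96 / 201.5 × 12 = 5.7 months, yet that section also concludes 9 months. Neither calculation counts families recruited through the mass media.

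**2. The 18-month total.** Minimum duration = recruitment + follow-up of the last family = 9 + 12 = 21 months. The stated total is short by 21 − 18 = 3 months. This is before the week allowed for posting the urine samples and the 7 days of accelerometer wear. The 18 months does not reproduce from the 9-month recruitment that both sections state. Only the unused 5.7-month figure would come close: 5.7 + 12 = 17.7 months.

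**3. What a stop at month 18 would mean.** Only families with baseline by month 18 − 12 = 6 reach the final visit. The protocol gives no accrual pattern. Taking the share enrolled by month t as (t/9)^k, the share missing the final visit is 1 − (6/9)^k:

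| Accrual shape | k | Share missing | Families of 96 | Left per arm, before attrition |
| --- | --- | --- | --- | --- |
| Front-loaded | 0.5 | 18% | 17.6 | (96 − 17.6)/2 = 39 |
| Uniform | 1 | 33% | 32 | (96 − 32)/2 = 32 |
| Back-loaded | 2 | 56% | 53.3 | (96 − 53.3)/2 = 21 |

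The plan needs 38 per arm after attrition. Its own allowance is 1 − 38/48 = 20.8%. Under uniform accrual the 32 per arm is below 38 before any attrition. Under the front-loaded shape the 39 per arm leaves almost no room for it.

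**4. What would remain.** The last family enters at month 9 and reaches its 14-week visit at about month 12 (14 weeks is about 3.2 months). BMI, waist and skinfolds at 14 weeks would therefore be available for all entrants who attend. Deuterium fat mass is the only component of the main parameter with no other post-baseline value.

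**5. End-of-study definition.** The only home visits described are optional information visits before consent. Baseline and follow-up measurements are taken at the Municipal Health Service. Read literally, the end of study is tied to an event that comes before a family's baseline.

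**The case against.** The strongest reply is that the duration sentence is descriptive. It sets no data cut-off, truncates nobody's follow-up and ends no participation by calendar date, whereas the 12-month measurement is specified repeatedly and without exception for late entrants. The sponsor would most likely run on until the last final visit. That stands. A reader might infer that a third of families cannot have their 12-month outcome, but the documents support this only if month 18 is enforced, and the one-third figure further assumes uniform accrual.

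A reader might also infer a definite loss of power. The documents do not support a figure. The Sample size section gives no standard deviation, so any standardised effect would have to be solved backwards from 38 per arm. The effect stated there is 0.30 BMI-points over 6 months, not a 12-month BMI z-score. Families without the final visit would still contribute 14-week values.

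It can also be said that the protocol shows a conflict without showing which figure is wrong. The 6-month references in Study procedures and in the sample size effect suggest that 18 months could be left over from a shorter follow-up (9 + 6 = 15 months would fit). That is only an inference, and it is a reason to reconcile the sections.

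Finally, the recruitment inputs do not cause the 18 versus 21 conflict, since both sections state 9 months. Nothing ties data collection to the last home visit; the definition governs reporting to the ethics committee. Both are secondary.

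None of this removes the arithmetic: the stated total is 3 months too short for the recruitment and follow-up that the same document plans.

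**Conclusion.** The point holds as an internal inconsistency. The protocol's own recruitment and follow-up periods need at least 21 months, plus about a week for samples and accelerometers, against a stated 18. The 3-month gap rests on no assumption beyond the protocol's figures.

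The consequence is conditional. If month 18 were enforced and accrual were uniform, 32 of 96 families (33%) would lose the 12-month BMI z-score and any post-baseline deuterium value; the range is about 18% to 56% over the accrual shapes tried. No loss of the primary outcome is demonstrated, and no power figure should be claimed.

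**What to change.** - **Main correction.** Restate the total duration in Study design as at least 21 months plus sample return. Alternatively, justify recruitment in 6 months or less and change both 9-month statements to match.
- **Follow-up timing.** Reconcile the 6-month deuterium entry under Study procedures with the 12-month timing elsewhere, so that the duration rests on one follow-up time.
- **Recruitment inputs (secondary).** Use one set in Population (base) and Sample size calculation: one age range, one eligible share, and a statement of whether 2600 is a yearly flow.
- **End of study (secondary).** Replace the last home visit with the last 12-month measurement, whether defined by the visit or by sample return.

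The cost is protocol wording, notified to the ethics committee as an amendment. If the 9-month recruitment stands, the three extra calendar months are already required by the 12-month visit.
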